## Abstract

**Introduction:**

Breast screening uptake remains low in parts of the UK, partly due to barriers including limited transport access. Offering free transport to screening appointments may help address this and improve uptake. This general practitioner (GP) cluster-randomised feasibility trial will assess whether offering free door-to-door transport alongside routine screening invitations increases attendance.

**Methods and analysis:**

Eight general practices in Yorkshire will be randomised to either the intervention (routine invitation plus information about booking free door-to-door transport) or control (routine invitation only) group. Around 8000 women due for routine breast screening will be included. Primary feasibility outcomes include GP recruitment and randomisation, intervention fidelity, proportion of women from the 10% most deprived areas, acceptability and data transfer processes. Secondary outcomes include understanding travel behaviour, cost-effectiveness and screening uptake. Data will be collected from routine National Health Service (NHS) screening records, data linkage with NHS England, travel surveys and qualitative interviews exploring experiences and acceptability. Patient and public involvement is embedded throughout with members contributing to advisory and oversight roles.

**Ethics and dissemination:**

The trial has received ethical approval from the London–Harrow Research Ethics Committee, Section 251 approval from the Confidentiality Advisory Group and other relevant regulatory bodies. The University of Hull is the study sponsor. Results will be disseminated through peer-reviewed journal publications, conference presentations and plain English summaries for participants and the public. Findings will inform the feasibility and design of a potential larger trial to improve breast screening uptake via transport support.

**Trial registration number:**

ISRCTN17087898.

STRENGTHS AND LIMITATIONS OF THIS STUDYRobust study design that will produce data to support regulatory approval.The statistical analysis methods are appropriately chosen, ensuring reliable and valid results.It may not be possible to interview a sufficient number of women who did not attend the screening due to a lack of interest in participation.

## Introduction

 Breast cancer is the most commonly diagnosed cancer among women in the UK and in Yorkshire alone around 4300 women are diagnosed with breast cancer each year.^1^ Survival is closely linked to stage at diagnosis: 5-year survival for women diagnosed at Stage I is 97.9%; but falls sharply to 26% for those diagnosed at Stage IV.^2^ The National Health Service (NHS) breast screening programme was introduced to promote earlier detection, thereby improving survival outcomes.^3^ All women aged 50–70 years old are invited for breast screening every 3 years, yet uptake remains suboptimal. Yorkshire is a large region in northern England, comprising urban and rural areas with a diverse population. In Yorkshire, only 71.4% of eligible women attended their most recent screening appointment, with significant variation across the region.^4^ National data indicate that on average, 8.4 breast cancers are detected per 1000 women screened.^5^ Based on this rate, approximately 197 000 women did not attend screening in Yorkshire over a 3-year period, representing an estimated 1655 potentially detectable cases of breast cancer that may have been diagnosed at an earlier stage.^4 5^ Public Health England identifies 70% attendance as an acceptable threshold, but 80% as achievable.^6^ While Yorkshire marginally exceeds the acceptable level, it falls short of the achievable benchmark, with notable disparities in screening uptake across the region. Addressing barriers to participation is therefore a public health priority, particularly in areas of high deprivation and poor access to services. Improving uptake has the potential to significantly impact early detection and survival outcomes across the region.

Non-attendance at breast screening appointments is influenced by a range of factors, including a perceived lack of personal risk, cultural and religious beliefs, previous negative experiences, language barriers, embarrassment and practical difficulties in accessing the screening site.^7^,^9^ One of the most commonly reported barriers is limited access to screening facilities—either directly (eg, due to transport costs) or indirectly (eg, competing time commitments). Several studies have found that women who live further away from breast screening sites are significantly less likely to attend.^10 11^

One possible approach for increasing screening uptake rates is to target interventions that ensure women can get to breast screening facilities ‘…at reasonable cost, in reasonable time and with reasonable ease’.(p6)^12^ The introduction of mobile breast screening vans targeting reducing the distance needed to travel by bringing breast screening facilities to local communities has been one potential solution to this issue.^10^ However, constraints on where they can be located due to the van size, need for access to electricity and parking for operational staff and attendees have resulted in them not always being located in sites that are easy to get to without a car, or are based in areas unfamiliar to the women who need to attend.^7^ Additional measures such as providing transport to reduce the physical barrier between home and screening site are still needed to allow some women to attend their appointment.

Providing free door-to-door transport to support access to healthcare appointments for individuals facing mobility or logistical challenges is not a new concept. The Yorkshire Ambulance Service alone conducts approximately one million non-emergency journeys each year, transporting patients to hospital appointments.^13^ However, women invited for routine breast screening are not eligible for this transport provision.^14^ Several studies have explored interventions to improve access to screening services, including the use of taxis, bus passes and transport vouchers.^15^,^17^ For example, Bell *et al*^16^ implemented a multicomponent intervention in three inner-city Cardiff general practitioner (GP) practices, which included the offer of transport to the screening centre. The intervention was associated with a 15% increase in attendance compared with previous screening rates within those practices. However, this study was not a randomised controlled trial, lacked a comparison group and did not isolate the effect of transport from other components of the intervention package. We hypothesise that offering a free, convenient, door-to-door transport service will improve breast screening attendance in Yorkshire, particularly among underserved populations. At present, there is insufficient evidence to inform commissioning decisions regarding transport support for breast screening attendance. A large-scale trial would be required to provide robust evidence of effectiveness and cost-effectiveness and subsequent commissioning of door-to-door transport. To address some of the uncertainties about the delivery of a definitive trial, we are undertaking a feasibility trial. This trial aims to assess the acceptability, fidelity and potential impact of a dedicated transport intervention on breast screening uptake.

## Methods and analysis

This protocol was prepared in accordance with the SPIRIT (Standard Protocol Items: Recommendations for Interventional Trials) 2013 reporting guidelines.^18^

### Study aims and objectives

This feasibility trial is a necessary first step to evaluate the practicality of trial procedures, the fidelity of intervention delivery and to provide preliminary signals of effectiveness, estimate cost effectiveness and generate data to inform sample size calculations for a future definitive phase III randomised controlled trial.

The primary aim of this study is to assess feasibility across key domains:

Recruitment of GP practices.Implementation of the intervention.Data collection processes.Acceptability of the intervention.

In addition, the study will:

Provide an initial indication of efficacy.Generate preliminary cost-effectiveness data.Inform the design and sample size calculations for a potential definitive phase III randomised controlled trial.

Screening attendance data will be obtained from the NHS Breast Screening Service (NHS BSS) and this will be linked via NHS England through the Data Access Request Service (DARS) to deprivation and ethnicity data.

Travel surveys will be administered to participants in both the intervention and control arms to explore how women travel to screening appointments. To further assess the acceptability of the intervention, a subset of women from the intervention group—as well as representatives from the transport provider—will be invited to participate in qualitative interviews. These interviews will explore experiences of the transport offer, barriers or facilitators to use and perceptions of acceptability.

### Study design

The intervention is the offer of free door-to-door transport to a routine breast screening appointment for all eligible women registered at GP practices randomised to the intervention arm of the trial. All women registered with GP practices in the intervention arm, who are due to be invited to routine breast cancer screening within the intervention time window, will be given information on how to book transport to their appointment. The information will be delivered through a letter (detailing the offer) that is included at the same time as the routine screening invite letter sent by the Humber and East Yorkshire (HEY) BSS. The transport offer will include being driven from home (or workplace) to the appointment; the driver will wait for the appointment to finish and drive the participant back. Taxi companies based in the two areas of East Riding of Yorkshire (ERY) and Kingston-Upon-Hull (Hull) will be used. The transport provider will provide transportation services, including any drivers licensed to carry out private hire bookings in accordance with the private hire vehicle regulations. The trial will cover the costs of the journeys.

The free transport will be offered with the first HEY BSS screening invitation letter sent to the women at an intervention GP. If the women do not attend the first appointment offered, then a second invitation will be sent routinely from the screening service and free transport will again be offered at this stage. If the women do not attend the second appointment offered by the HEY BSS, then no further appointment will be sent by the screening service. The women can then use the free transport up to 6 months from the first invitation letter if they subsequently book the screening appointment themselves.

If any of the participants in the intervention arm need a recall for a further screening assessment, they can also still use the free transport offer.

Figure 1 outlines recruitment, randomisation, participant flows and data collection (see separate document uploaded for Recruitment, randomisation, participant flows and data collection).

**Figure 1 F1:**
[figure not shown]
Recruitment randomisation, participant flows and data collection. GP, general practitioner.

### Study population

The study is a cluster randomised feasibility trial, with clustering at the level of the GP practice. Eight GP practices will be included in this study. GPs will be allocated to the intervention group or the control group. The flow of participants is shown in figure 1 (see separate document uploaded for Recruitment, randomisation, participant flows and data collection). A GP cluster randomised design has been proposed instead of individual patient level randomisation for two reasons: the complexity of individual randomisation and preparation of letters with/without transport information for the screening service; and the letter inviting women to book transport may be shared or discussed between women who are registered at the same practice or live in the same area, leading to trial contamination. Known issues of requiring larger sample sizes and recruitment bias in cluster randomised controlled trials (RCTs) are mitigated as all women at intervention practices will receive the intervention letter and anonymised routinely collected outcome data are being obtained.^19^

Women at participating GP practices will receive the standard screening invitation letter at the usual planned time from the screening service, with women registered at an intervention GP practice receiving additional information about the transport booking instructions. A participant notification poster will be displayed at GP practices during the trial.

We estimated 8000 participants will be included in the trial based on the number of eligible women (between ages 50 and 70) at eight average sized GP practices. This estimate was derived from internal data provided by the local BSS in which the study is being conducted. The sample size of eight practices will allow for the reliable estimation of key feasibility figures and detection of signals of efficacy for the future full trial.^20^

### Study recruitment

The eight GP practices from ERY and Hull will be identified with the support of the local Clinical Research Network (CRN) and the HEY BSS schedules. The schedule for inviting women for breast cancer screening from GP practices is determined 3 years in advance, running on a 3-yearly rota. GP practices whose registered women are scheduled to be invited in the 12-month intervention phase of the study will be selected to participate. All women invited for a routine breast screening appointment who are registered at the selected practices will be included in the trial. The HEY BSS has one permanent screening site at Castle Hill Hospital and two mobile vans that serve ERY and Hull. Women are invited to attend the site closest to their registered GP and the permanent site if they have mobility issues that mean climbing stairs is not possible or have additional needs.

### Intervention arm

Women registered at an intervention GP practice will receive the standard screening invitation letter at the usual planned time from the screening service with an additional approved information sheet included detailing instructions for booking the free door-to-door transport. This supplementary sheet will be included with the routine invitation letter posted to women by the BSS. Women are invited to attend the specific mobile unit or hospital site that is closest to their GP practice at the time of the initial invite. If participants in the intervention arm require a follow-up screening assessment, they can continue to use the free transport service.

All women in the intervention arm who attend the screening appointment will be asked to complete an intervention travel survey when they attend. 30 women in the intervention arm will be recruited for qualitative interviews to understand their experiences and perceptions of the door-to-door transport intervention.

### Control arm

Women at participating GP practices will receive the standard screening invitation letter at the usual planned time from the screening service. Women in the control arm who are attending their appointment will also be asked to complete a control arm travel survey when they attend their screening appointment.

### Eligibility criteria

Inclusion criteria:

GPs located in ERY or Hull.Whose registered women meet the age criteria for the national breast screening programme (between 50 and 70 years old) and are due to be invited to attend a routine screening appointment during the intervention window.

Exclusion criteria:

GP practices located outside of the set geographical area.Women with non-routine screening appointments.

### Randomisation

GP practices will be randomised 1:1 to the intervention arm or control arm with variable block sizes, stratified by area deprivation. Randomisation will be completed via the REDCap Cloud (RCC) online system provided by the Hull Health Trials Unit (HHTU).

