### Sample size

The study sample size is estimated as 8000 women from eight GP practices. This is a pragmatic sample size based on the number of eligible women (between the ages of 50 and 70) at eight average sized GP practices. This sample size will allow for the reliable estimation of key feasibility figures and detection of signal of efficacy for the future full trial.^20^

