### Primary outcomes

The primary feasibility outcomes are summarised in table 1 along with criteria that will be used as a guide for progression to a future definitive phase III trial and described here:

Number of GP practices that agreed to participate and were randomised ahead of the scheduled breast screening invitation window.Percentage of women invited from GP practices located in the 10% most deprived areas.Percentage of intervention invites sent out by the BSS to all women during the scheduled breast screening invitation window.Percentage of women who requested transport who were transported to and from their appointment by the service.Acceptability of the intervention to the women and the service providers.Completion and transfer of the screening and transport service data when required for analysis.

**Table 1 T1:** Primary outcomes to assess feasibility and progression criteria

Feasibility outcomes	Outcome measure	Green	Amber	Red
Recruitment and randomisation of GP practices	Number of GP practices that agreed to participate and were randomised ahead of the scheduled breast screening invitation window.	8 (planned number of practices)	6–7 (numbers may still be achieved if invitations sent during part of the period, or less practices with more women)	<6 (insufficient number of practices/women included to provide data for sample size and feasibility estimates)
	Percentage of women invited from GP practices located in the 10% most deprived areas.	30%	15–30%	<15%
Fidelity of the transport intervention	Percentage of intervention invites sent out by the BSS to all women during the scheduled breast screening intervention window.	100% (all four intervention sites)	75%	<75%
Fulfilment of requests for the transport intervention	Percentage of women who requested transport who were transported to and from their appointment by the service.	100%	50–99% (explore reasons such as too many appts same date/time)	<50% (not viable to increase or change transport service to meet the demand)
Acceptability of the intervention to the women/service providers	Qualitative interviews.	Acceptable to all interviewed and no major barriers identified.	Acceptable with some modifications	Not acceptable to the majority of people interviewed
Completion and transfer of screening and transport service data when required for analysis	Screening service attendance data.	Screening data provided for all women in both arms of the trial.	Partial data provided	Data has not been transferred

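### With eight practices, variable blocks within deprivation strata do not secure the 4:4 split that Table 1 takes as given

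*Protocol article*

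**What the plan says.** The number of clusters is fixed. Study population says "Eight GP practices will be included in this study", and the green level for recruitment in Table 1 is "8 (planned number of practices". The allocation method is one sentence under Randomisation: "GP practices will be randomised 1:1 to the intervention arm or control arm with variable block sizes, stratified by area deprivation". Table 1 then treats the result of that method as known, since the green level for intervention fidelity reads "100% (all four intervention sites", with amber at 75% and red below it.

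The article does not give the block sizes, the number of deprivation strata or the number of practices in each. Nothing in it restricts the overall allocation to four and four. On scale, the Sample size section says "The study sample size is estimated as 8000 women from eight GP practices" and calls this pragmatic; it states no power, significance level or target effect. Screening uptake is a secondary outcome, examined for a possible signal of efficacy.

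**The concern.** Permuted blocks give equal arms only when every block is completed. With many units, one unfinished block per stratum is negligible. With eight units spread over two or more strata, it is a large part of the trial. Mixing block sizes makes an unfinished block possible even in a stratum with an even number of practices, and an odd-sized stratum always leaves one.

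Two things are at stake. First, the plan relies on a four-site intervention arm that its method does not deliver with certainty. Second, an unfinished block unbalances the arms within a deprivation level, which is what the stratification is there to prevent. Deprivation matters in this trial: it has its own progression criterion in Table 1, uptake is to be reported by it, and the equity analysis under Health economics depends on it.

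**Working it through.** **Inputs from the article.** Eight practices, 1:1, variable blocks, deprivation strata. The intended intervention arm is 8 × 1/2 = 4 practices, which reproduces Table 1's four sites as the planned split.

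**Assumptions, because the article is silent.** Block sizes are equally likely within {2,4} or {4,6}. Strata are 4+4, 5+3 or 3+3+2. The last block is cut off when the stratum is full.

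**Formula.** If a block of size b is cut after n practices, the number x sent to intervention is hypergeometric: P(x) = C(b/2, x) × C(b/2, n−x) / C(b, n). The strata are independent and their counts are added.

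**Strata 4+4, blocks {2,4}.** A stratum fails to split 2:2 only if the first block is 2 (probability 1/2), the second is 4 (1/2), and the first two places of that second block go to the same arm (1 − 4/6 = 1/3). That is 1/2 × 1/2 × 1/3 = 1/12, divided equally between 3:1 and 1:3 (1/24 each). The overall split is 4:4 if both strata are even or if their imbalances cancel: (11/12)² + 2 × (1/24)² = 0.844. The chance of a miss is 16%.

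**Strata 4+4, blocks {4,6}.** A stratum fails only if the block is 6 (1/2) and its first four places are not 2:2 (1 − 9/15 = 0.4). That is 0.20, or 0.10 each way. P(4:4) = 0.80² + 2 × 0.10² = 0.66. The chance of a miss is 34%.

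**Strata 5+3, blocks {2,4}.** The stratum of five gives 2 or 3 to intervention with probability 1/2 each, and the stratum of three gives 1 or 2 with probability 1/2 each. The total is four for 2+2 or 3+1, so P(4:4) = 1/4 + 1/4 = 0.50.

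**Chance of missing 4:4, by exact enumeration.**

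| Strata | Fixed blocks of 2 (comparison) | Blocks {2,4} | Blocks {4,6} |
|---|---|---|---|
| 4+4 | 0% | 16% | 34% |
| 5+3 | 50% | 50% | 53% |
| 3+3+2 | 50% | 54% | 62% |

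The comparison column separates the two causes. In even strata, the risk comes from mixing block sizes. In odd strata, it is almost all there already with fixed pairs.

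Even with no strata, P(4:4) is 0.90 for {2,4} and 0.72 for {4,6}. None of the variable-block scenarios enumerated gave certainty.

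**Size of the miss.** Over the two-strata splits enumerated (4+4, 5+3, 6+2, 7+1), the chance of 6:2 or worse is 0% to 3%. With 3+3+2 it is 4% ({2,4}) to 13% ({4,6}).

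**Precision.** For practices of equal size and equal variance, the variance of the arm contrast relative to 4:4 is (1/a + 1/b) / (1/4 + 1/4).
- 5:3: (1/5 + 1/3) / 0.5 = 1.067, so variance +7% and standard error about +3%.
- 6:2: (1/6 + 1/2) / 0.5 = 1.333, so variance +33% and standard error about +15%.

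**Deprivation balance.** With strata 4+4, the chance that at least one stratum splits unevenly is 1 − (11/12)² = 16% for {2,4} and 1 − 0.80² = 36% for {4,6}.

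**The case against.** The strongest reply is that the harm is small. The usual miss is 5:3, which costs about 3% in standard error, in a feasibility trial with a pragmatic sample and no powered test. That stands, and it limits the severity.

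A second reply is that the full protocol may hold block sizes and strata that reduce the problem. Their absence from an article is no fault. But no variable-block set tried gives certainty. Certainty needs a fixed block size that divides every stratum, and the article says the sizes vary.

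Four stronger readings are tempting, and the article does not support them.

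- *Variable blocks cause the 50% to 62% figures.* They do not. With 5+3 or 3+3+2, fixed pairs miss 4:4 half the time as well.
- *An uneven split makes the Table 1 fidelity criterion unusable.* The measure is a percentage of invitations sent, and it can be computed with three or five sites. The reference to four sites is a gloss on the green level. Only if the bands are read in whole sites does the number matter: one failed site of four is 75% (amber), of three 67% (red), and of five 80% (in no stated band).
- *Variable blocks have no use here because the rota is known.* Study recruitment does say that "The schedule for inviting women for breast cancer screening from GP practices is determined 3 years in advance". That shows when practices are due, not whether they have agreed. If they join one by one, concealing the next allocation still has value.
- *The scheme is wrong to omit previous uptake and list size.* One stratification factor is reasonable for eight clusters, and previous uptake is already planned as a benchmark. Balancing on more factors is a preference.

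**Conclusion.** The point holds in a limited form. The stated method aims at 4:4 but does not secure it, while Table 1 writes the four sites in as settled. The chance of a different split is about 16% to 34% if the strata are 4+4, and about 50% to 62% if they are 5+3 or 3+3+2. These figures rest on assumed block sizes and strata. The qualitative conclusion does not depend on which of the variable-block sets tried is used.

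The consequence is usually a modest loss of precision and some loss of deprivation balance, and only occasionally a 6:2 split. Nothing here invalidates the trial or its feasibility outcomes. Minor to moderate severity.

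**What to change.** **If allocation is still to come.** Sign up the practices first. Then make one random draw from the allocations that give exactly 4:4 overall and split each deprivation stratum as evenly as possible. Enough allocations remain: with two strata of four, C(4,2)² = 36; with 5+3, C(5,3) × C(3,1) + C(5,2) × C(3,2) = 30 + 30 = 60. If fewer than eight practices agree (Table 1 allows for six or seven), apply the same rule with the arms as equal as the number permits.

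**If practices must enter in turn.** Constrain the list so that the overall total is 4:4. Fixed pairs within stratum are not enough, because they miss 4:4 half the time when strata are odd-sized. The cost is that the last allocations can become predictable, so the list should be held away from those who approach practices.

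**If allocation is already done.** This is possible, since Current trial status says that recruitment opened in August 2024 with a 12-month window. Report the actual split overall and by stratum, adjust the uptake comparison for deprivation stratum, and restate the Table 1 fidelity criterion for the actual number of intervention sites.

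**Cost.** The preferred option changes only how the allocation is generated. Its real downside is that the practices must agree before the draw, which may delay the first ones.
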